#### Provider training and fidelity

3.3.3.

ROSE is designed to be a flexible, adaptable program that requires minimal training to deliver [56]. The five La Luz co-facilitators to date are bilingual psychologists or social workers experienced with working with the perinatal population. The facilitators are supervised by [name], a licensed clinical psychologist and an experienced supervisor trained in ROSE, via monthly supervision meetings to ensure the quality and fidelity of intervention delivery. La Luz facilitators were trained in one of three ways (each took approximately four hours): (1) virtual training conducted by the developer of ROSE (two facilitators); (2) in-person training conducted by an experienced facilitator of La Luz at Thriving Families, a local non-profit that also offers La Luz, following the standard ROSE training protocol (two facilitators); or (3) online training available through the official ROSE program website [56] (one facilitator).

### Evaluation of implementation process and outcomes

3.4.

Evaluation of the implementation of La Luz will occur quantitatively and qualitatively in this study, guided by Proctor’s implementation outcomes framework [57] and the Integrated Promoting Action on Research Implementation in Health Services (i-PARIHS) model [58]. Proctor’s framework operationalizes the goals of quality evidence-based mental healthcare, including perceived feasibility, acceptability, and appropriateness of treatment, and costs of the intervention [57]. The i-PARIHS guides qualitative measurement of the implementation process and focuses on three elements that drive successful implementation of an intervention: innovation, recipients, and context [58]. Table 1 provides definitions of constructs of these two frameworks.

Approximately 30 participants (12–15 per delivery modality) will be recruited to complete focus groups (in English and Spanish) within 6 months of completing the fourth La Luz group session. Focus groups use a semi-structured in-depth format with open-ended questions and last approximately 60 min. The focus groups explore themes relevant to i-PARIHS constructs: 1) perceived challenges and barriers, including perceived cultural relevance and barriers, to session attendance and engagement with the intervention material and content; 2) perceived risks and benefits of the treatment modality received (i.e., in-person vs virtual) for perinatal depression; 3) perceived appropriateness and fit of the intervention and delivery modality to participants’ specific needs; and 4) perceived skills and benefits derived from the intervention. Focus groups will also be conducted with approximately 10 hospital providers, staff, and administrators after enrollment into the RCT ends; these focus groups assess constructs similar to those assessed in the participant focus groups regarding implementation drivers, with a focus on sustainability of the program in the setting after the research study ends.

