**Fig. 2. F2:**
[figure not shown]
Superiority, non-inferiority, and equivalence trials. *Note*. This figure shows the relationship between superiority, non-inferiority, and equivalence trials. The negative and positive margins (−*d* and +*d)* indicate the confidence intervals set to establish the effect of the intervention.

**Table 1 T1:** Measurement of implementation progress and outcomes.

Proctor’s outcomes [57]	Definitions and measures
Acceptability	*Definition*: the perception that the intervention is agreeable, palatable, or satisfactory among stakeholders *Measures*: 4-item Acceptability of Intervention Measure [73] (e.g., “The program is appealing to me”)
Appropriateness	*Definition*: perceived fit, relevance, or compatibility of the intervention for a given practice setting, provider, or consumer or for addressing a particular issue *Measures*: 4-item Intervention Appropriateness Measure [73] (e.g., “The program seems like a good match for me.”)
Feasibility	*Definition*: the extent to which the intervention can be successfully carried out within a given agency or setting *Measures*: 4-item Feasibility of Intervention Measure [73] (e.g., The program seems doable to me.”) Recruitment metrics: time from study start to completion of recruitment, number of referrals to the study, and numbers of eligible and ineligible participants
Cost of implementation	*Definition*: cost impact of an implementation effort, which depends on depends on the costs of the intervention, the implementation strategy, and the location of service delivery. *Measures*: Structured interviews with personnel involved in administration of the intervention and assessment of resources to quantify cost of in-person and virtual ROSE Self-report data from patients on their use of all types of health services (inpatient, outpatient, pharmacy) EHR data from Denver Health on all types of service, service dates, beneficiary copayment, and primary and secondary ICD-10 and CPT4 codes for each episode of care over the 12-month period after completion of ROSE (after the postpartum booster) and for the 12-month period preceding pregnancy (and before participating in ROSE). Short-term increase in cost due to reductions of barriers to care evaluated via the Barriers to Access to Care Evaluation (BACE) [74], which is a 30-item comprehensive evaluation of barriers to obtaining mental health care and have good test-retest reliability and internal consistency.

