i-PARIHS constructs [58]	Definition and measures
Innovation	*Definition*: assesses scientific research evidence against existing practice (e.g., the usability of the research evidence, its compatibility with existing policies and practices, its clarity) *Focus groups with the following example questions*: How well do you see the program meeting your needs? (for patients) What did you like about receiving the program in-person/virtually? (for patients) How well does the program fit into your existing services? (for administrators)
Recipients	*Definition*: takes a broad view of the individuals involved in the implementation process and includes patients/clients, providers, and clinic managers. *Focus groups with the following example questions*: How did the program address your cultural background? (for patients) How did the program fit into your daily life? (for patients) How did the program disrupt your usual work flow? (for providers)
Context	*Definition*: includes the immediate context (e.g., a clinical team, service, or clinic) and the outer context in which the clinical setting is embedded (e.g., the organizational infrastructures surrounding the clinic). *Focus groups with the following example questions*: Where would a program like this need to take place for you to feel interested and comfortable accessing it? (for patients) What things in your life got in the way of participating in the program in the way you would have liked? (for patients) What barriers do you see to maintain this program after the study ends? (for administrators)

*Note*. This table summarizes key implementation process and outcomes that will be assessed by the current study.

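### Participant focus groups and the post-programme health-record window are anchored to completing La Luz, so people who did not complete it fall outside these two sources

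*Protocol article*

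**What the plan says.** Section 2 lists barriers among the Aim 2 outcomes. It also says that the programme's effect on service use will be explored and its cost documented.

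Section 3.4 describes the participant groups: about 30 people, 12 to 15 in each modality, "will be recruited to complete focus groups (in English and Spanish) within 6 months of completing the fourth La Luz group session". Their first topic is "perceived challenges and barriers, including perceived cultural relevance and barriers, to session attendance and engagement with the intervention material and content". Table 1 (Context row) gives a matching example question for patients: "What things in your life got in the way of participating in the program in the way you would have liked".

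Table 1 (Cost of implementation row) sets two periods for health-record service and cost data: "over the 12-month period after completion of ROSE (after the postpartum booster") and "for the 12-month period preceding pregnancy (and before participating in ROSE"). The same row also lists self-reported service use and the Barriers to Access to Care Evaluation (BACE).

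Four other places bear on the point:
- Section 3.3.2 allows missed sessions to be made up, and gives the booster individually and virtually in both arms.
- Section 3.5.1 ties the surveys to gestational and postpartum dates, and collects care utilisation from health records with no condition on attendance.
- Section 3.6.1 plans a sensitivity analysis restricted to completers, so the authors expect some non-completion.
- Section 3.7 uses the barriers identified to build the toolkit.

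**The concern.** The people best placed to say what stops attendance are those who never came or who stopped early. A focus-group sample timed from completing session four does not reach them. It hears from people whose barriers could be overcome, and the toolkit would inherit that tilt. For a programme justified by access, the missing group is the one of most interest.

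The record window has a related weakness. A participant without a booster has no date from which to count 12 months. Those with a booster start at whatever point after birth it took place, so the same 12 months covers different stretches of the postpartum year and beyond. Completion follows randomisation and may depend on modality. Figures by modality from this window would therefore describe selected subsets of each arm, not the arms as randomised.

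**Working it through.** The article states no figure on this point, so there is none to reproduce. The check sets the sources side by side and then shows how the number affected depends on an unstated rate.

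**Which Aim 2 participant-level sources depend on completion**

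| Source | Where | Anchor | Covers a non-completer? |
|---|---|---|---|
| Participant focus groups | 3.4 | Completing session four | No date given |
| Health-record costs, after programme | Table 1 | Completion, after the booster | No date given |
| Health-record costs, before | Table 1 | Pregnancy | Yes |
| Self-reported service use | Table 1 | No completion condition | Yes |
| BACE (30 items) | Table 1 | No completion condition | Yes |
| Acceptability, appropriateness and feasibility scales | Table 1 | No completion condition | Yes |
| Health-record care utilisation, general | 3.5.1 | No completion condition | Yes |

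Two of the seven rows depend on completion. The question is whether the other five fill the gap.

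- *Barriers to attendance.* BACE concerns barriers to mental health care in general, not to La Luz sessions. The scales ask how the programme is perceived. As described, the participant focus groups are the only source that asks participants what got in the way of attending this programme.
- *Use of care.* Self-report and general record utilisation can cover non-completers, so the data may well exist. The defect is in the period that Table 1 defines for the cost item. It opens after the booster, and the earlier period closes at the start of pregnancy, so the time from conception to the booster lies in neither.

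**Size, under assumption**

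Inputs: target 900 (section 3.1.1); focus groups 2 × 12 = 24 to 2 × 15 = 30 (section 3.4). Let q be the assumed proportion who miss the anchor. It has to be taken separately for session four and for the booster, which are different events.

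- Participants with no defined date = 900 × q.
- Non-completers expected among 30 people drawn at random from all randomised = 30 × q.

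| Assumed q | 900 × q | 30 × q | In the focus groups as written |
|---|---|---|---|
| 0.10 | 90 | 3 | 0 |
| 0.20 | 180 | 6 | 0 |
| 0.30 | 270 | 9 | 0 |
| 0.40 | 360 | 12 | 0 |
| 0.50 | 450 | 15 | 0 |

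The 20% in section 3.1.1 is loss from the study, not failure to finish the programme. It cannot be used for q.

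**The case against.** The best defence is that the session-four wording sets timing and is not an eligibility rule. An article need not give the full sampling frame for about 30 qualitative participants. Someone who missed earlier sessions but completed the fourth is still inside the window, and make-up sessions shrink the group outside it. Three of the four topics (modality, fit, skills gained) presuppose some exposure, so a preference for attenders is understandable. The booster is virtual for everyone, which weakens the argument that modality drives who receives it.

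Much of this stands as a limit on the point. It does not remove it: even as pure timing, the rule gives no date for a person who does not complete session four, and the first topic is attendance itself. The record window has the same gap, and the table fixes it explicitly.

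A reader might infer four stronger things that the article does not support:
- *That Aim 2 as a whole leaves out non-completers.* Five of the seven sources above carry no completion condition.
- *That care between randomisation and the booster is not collected.* Only the Table 1 record-cost item skips it. Section 3.5.1 and self-report are not so limited.
- *That a biased test between arms is planned.* Section 2 speaks of exploring utilisation, and section 3.7 looks at implementation outcomes separately by modality. No formal comparison of utilisation is specified.
- *That the before-and-after contrast is an unrecognised flaw.* The Discussion already acknowledges, for clinical outcomes, that there is no arm without ROSE. The same missing comparator applies here.

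**Conclusion.** The point holds for two sources only. As written, the participant focus groups explore attendance barriers among people who reached session four. The post-programme record window is undefined for anyone without a booster and starts at varying times for the rest. Any description by modality from that window is conditioned on a post-randomisation event.

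The number affected is unknown. The 90 to 450 range rests wholly on assumed rates of 10% to 50%, and make-up sessions push it down by an unstated amount. The direction of any distortion by modality cannot be told from the article. Severity is minor to moderate: the primary outcome and the non-inferiority test are untouched, but what Aim 2 can say about barriers to attendance and about service use is weakened. The verdict assumes that the text will be followed as it stands. If the full protocol already samples low attenders or gives other dates, the article's wording alone needs correcting.

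**What to change.** **Focus groups.** Keep the same roughly 30 places. In each modality, purposively invite some participants who attended none or only some sessions, and time invitations from the scheduled date of session four, which does not require having attended it. The exact share is a judgement for the investigators.

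**Record window.** Define the cost and utilisation periods by dates that do not depend on attendance, for example randomisation to delivery and delivery to 12 months postpartum, with a stated rule for a pregnancy that does not reach delivery. Keep the pre-pregnancy year. Summarise by randomised arm, whatever was attended. A period counted from the booster can stay as a supplementary description of those who had one.

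**Cost.** This needs revised wording in the recruitment procedure and the data extract, with no extra focus-group places and the same record source. Non-attenders may be harder to recruit. Fewer places remain for completers on the topics that need exposure to the programme. The article reports recruitment as ongoing, so the change could still apply to focus groups not yet held.

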### Measures

3.5.

#### Measures overview and schedule

3.5.1.

Participants complete self-report surveys via REDCap at seven assessment timepoints: before the program begins (baseline), at 28 gestational weeks, 35 gestational weeks, and at 6-weeks, 3-months, 6-months, and 12-months postpartum. Sociodemographic constructs are assessed at baseline and postpartum. Measures of mental health (e.g., depression severity) and other psychosocial constructs (e.g., social support) are assessed at each timepoint. Data are also collected from electronic health records for relevant constructs, including depressive symptoms and pregnancy-related information (e.g., gestational age, obstetric complications), and other health information (e.g., care utilization, medications). Participants receive $50 via a reloadable Visa card for each completed survey. They additionally receive a $50 bonus if they complete all three prenatal surveys and the 6-weeks postpartum survey, and another $50 bonus if they complete the 3-months, 6-months, and 12-months postpartum surveys.

#### Primary and secondary outcome measures

3.5.2.

##### Primary outcomes.

Depression symptoms are measured using (1) the 20-item Symptom Checklist (SCL-20) developed from the full Symptom Checklist-90-R [59], and (2) the 10-item Center of Epidemiologic Studies Depression Scale (CESD-10) shortened based on the original 20-item scale [60,61]. Both SCL-20 and CESD-10 are reliable and valid measures of depressive symptom severity, including with pregnancy participants [7,21,22,62]. For both scales, participants provided ratings using a 4-point scale on their symptoms for the past week (CESD-10) or month (SCL-20). Item scores for each scale are summed to generate a total score, with higher scores indicating higher depression severity. The SCL-20 and CESD-10 scores will be analyzed dimensionally as the primary outcomes of this RCT.

##### Secondary outcome.

Secondary analyses will involve evaluating depression assessed via the Edinburgh Postnatal Depression Scale (EPDS), which is widely used for screening maternal depression across the perinatal period [63]. Participants provide ratings on a 4-point scale on symptoms over the past week. Final sum scores range from 0 to 30, with higher scores indicating greater levels of depression. Previous studies support both good internal consistency (α > 0.80) and validity of the EPDS [64]. The EPDS has been validated among Spanish-speaking mothers [65]. The EPDS is standardly administered at the prenatal and postpartum medical visits at Denver Health. We collect EPDS scores from participants’ electronic health records to address real-world feasibility and sustainability of depression monitoring.

#### Implementation measures

3.5.3.

Quantitative and qualitative measures of implementation process and outcomes guided by Proctor’s framework [57] and i-PARIHS model [58] are summarized in Table 1.

### Analytic plan

3.6.

#### Analysis testing inferiority of virtual vs. in-person La Luz

3.6.1.

Primary analyses will use intent-to-treat design to evaluate the effectiveness of the intervention among all enrolled participants [66]. To test whether virtual La Luz will yield a similar benefit (i.e., is non-inferior) as in-person La Luz for perinatal depression, multilevel models (timepoints nested within participants) including random intercepts and slopes will be used. Multilevel modeling accounts for nested data structure and is robust to missing data [67]. In line with non-inferiority testing, we will use a one-sided test and statistical significance set at *p* < .05 with margin of non-inferiority set to an effect size Cohen’s *d* of 0.25 for our estimate contrasts of total change in our multilevel model. Model-based total change estimate will provide us flexibility if the change over time is nonlinear (i.e., log-linear, parabolic, piecewise, etc.). A negative effect size would indicate more reduction for virtual compared to in-person, whereas, a positive effect size would indicate more reduction for in-person compared to virtual. Non-inferiority will be shown if the effect size for contrast of total change yields a one-sided 95 % upper bound smaller than *d* = +0.25. If the one-sided 95 % upper bound is bigger than *d* = +0.25, the confidence interval for the true effect size of the contrast of total change does not lie totally within the non-inferior region, and non-inferiority cannot be concluded (illustrated in Fig. 2 with ±*d* as the indicated margins). Given that intent-to-treat approaches can bias non-inferiority trials toward finding the interventions to be non-inferior, we will also conduct a sensitivity analysis including only participants who complete the intervention [68,69]. Secondary analyses will follow the same analytic procedures but with EPDS scores collected from electronic health records as the outcome.

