## Abstract

Perinatal depression disproportionally affects underserved communities, who need effective and accessible prevention programs. Reach Out, Stay strong, Essentials for new mothers (ROSE) has demonstrated effectiveness in preventing postpartum depression in underserved populations when delivered in person. This ongoing randomized controlled trial (RCT) tests the novel virtual implementation of ROSE as universal prevention in a Federally Qualified Health Center setting. We adopted the name, La Luz, for ROSE to be culturally relevant to our population. Pregnant individuals <30 gestational weeks (target *N* = 900) are randomized to either the virtual or in-person La Luz program, which consists of four 90-min group sessions. Groups are offered in English and Spanish, based on participants’ preference. Participants complete surveys at seven timepoints: before program, 28 gestational weeks, 35 gestational weeks, and 6-weeks, 3-months, 6-months, and 12-months postpartum. Primary outcomes are postpartum depression severity measured by the 20-item Symptom Checklist (SCL-20) and 10-item Center of Epidemiologic Studies Depression Scale (CESD-10). We will perform intent-to-treat analysis to test whether virtual La Luz is non-inferior to in-person La Luz. This study also evaluates implementation process and outcomes of both modalities of La Luz to inform the development of an implementation toolkit. This RCT contributes to our knowledge of perinatal depression prevention and addresses access barriers for underserved populations. If effectiveness of virtual La Luz is demonstrated, the new evidence for a scalable low-cost prevention can be used to reduce perinatal depression and offer accessible treatment options for people who face significant barriers to care. Clinicaltrials.gov registration identifier: NCT05766475.

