#### Study population and recruitment site

3.1.1.

We aim to recruit 900 pregnant individuals from Denver Health obstetrics clinics. Pregnant individuals (18 years or older) who are English or Spanish speaking and at less than 30 gestational weeks are eligible. Individuals at 30 or more gestational weeks are excluded due to insufficient time to complete ROSE prior to delivery. The target sample size was determined based on power analyses accounting for an estimated 20 % attrition rate (10 % during pregnancy and an additional 10 % postpartum) and our primary analyses testing inferiority of virtual to in-person La Luz (see below).

Denver Health is a Federally Qualified Health Center serving low resourced and underserved pregnant individuals. The obstetrics clinics at Denver Health serve individuals from the surrounding urban metropolitan Denver area. Denver is a racially and ethnically diverse city, which is reflected in the Denver Health patient population. Among all patients who received care from Denver Health in 2023, 49 % identify as Hispanic/Latine, 13 % Black or African American, 30 % non-Hispanic White, and 4 % Asian or Pacific Islander [54]. Spanish-speaking patients make up a substantial portion of the Denver Health patient population, and some patients speak only Spanish [55].

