#### Virtual vs. in-person delivery

3.3.2.

We planned for the first four sessions of La Luz to be delivered prenatally in groups of 6 to 20, with a projected average of 12 per group. The group program is 90 min weekly for four weeks. The same facilitators co-facilitate the in-person and virtual modalities and across languages. Participants in both conditions are provided with workbooks by mail after their initial study intake appointment. Participants can complete any missed session by attending the session of a future cohort in the same modality or schedule an individual make-up session with the facilitator by phone or video. Following the birth of the baby, the individual booster session (typically 30–45 min) is scheduled with one of the facilitators. The booster session is delivered virtually for all participants (in both groups).

For in-person groups, transportation is provided to reduce barriers to attendance. For virtual groups, tablets with Zoom are provided to participants who need a video conferencing device. Transportation and tablets are provided to ensure that neither transportation nor technology were an inequitable barrier that negatively impacted participants’ perception or participation in the in-person or virtual groups. Participants in both conditions receive $10 for every group session they attend via a reloadable Visa card.

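### The primary model has no level for the therapy groups that deliver La Luz in both arms; if change is correlated within groups, non-inferiority will be declared too often

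*Protocol article*

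**What the plan says.** The protocol article (Abstract) states that participants "are randomized to either the virtual or in-person La Luz program, which consists of four 90-min group sessions". Section 3.2 describes individual allocation at the end of the baseline visit, when the first group session is also scheduled. Section 3.3.2 says the first four sessions are "delivered prenatally in groups of 6 to 20, with a projected average of 12 per group", and adds that "The same facilitators co-facilitate the in-person and virtual modalities and across languages". It also lets a missed session be made up with a later cohort of the same modality or individually, and the postpartum booster is individual.

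Section 3.6.1 sets the primary analysis: "multilevel models (timepoints nested within participants) including random intercepts and slopes will be used". It then credits multilevel modelling with handling nested data, but the only nesting it names is repeated measures within a person. The test is one-sided at the 5% level. The margin is stated in these words: "with margin of non-inferiority set to an effect size Cohen’s *d* of 0.25". It applies to the contrast between arms in total change. Non-inferiority is concluded when the one-sided 95% upper bound is below d = +0.25.

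Section 3.1.1 gives the target: "We aim to recruit 900 pregnant individuals from Denver Health obstetrics clinics". It says that this number comes from power calculations that allow for 20% attrition. Nowhere does the article mention a therapy-group effect, a cluster-robust variance, an ICC or a design effect.

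**The concern.** Randomisation is individual, but treatment is delivered to groups in both arms. Members of one group share sessions and interact with each other after randomisation, so their later changes in depression score may be correlated. The participant random intercepts and slopes do not capture this, because the model takes them as independent between people.

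Positive within-group correlation in change makes the model's standard error for the arm contrast too small. In a non-inferiority trial this works in the unsafe direction: the upper bound is too low, and a virtual programme that is truly worse by the margin passes more often than the stated 5%. The completer sensitivity analysis in section 3.6.1 addresses a different bias and gives no protection here.

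This is more than detail left to an unseen analysis plan. The article states the levels of the primary model, and they do not match the delivery described in section 3.3.2.

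**Working it through.** **Inputs from the protocol article.** 900 participants and 20% attrition (3.1.1), so 900 × 0.80 = 720 analysed. One-sided alpha 0.05 and margin d = 0.25 (3.6.1). Groups of 6 to 20, projected mean 12 (3.3.2).

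**Assumptions.** 1:1 allocation (the ratio is not stated), so 360 analysed per arm. SD of change = 1 on the d scale. True difference 0 for power. ICC of change from 0 to 0.10, because the article gives none.

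**The plan's own figure.** The power behind N = 900 is not stated, so the figure cannot be strictly reproduced. With n per arm = 2(z₀.₉₅ + z_power)²/0.25² and division of the total by 0.80, the enrolled total is 495, 578, 688 or 868 for 80, 85, 90 or 95% power. In reverse, 360 per arm gives SE = √(2/360) = 0.0745 and power Φ(0.25/0.0745 − 1.645) = 95.6% under full independence.

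**Analysed group size.** 900/12 = 75 groups, and 720/75 = 9.6 analysed per group. Twelve analysed per group is used as the upper value. It corresponds to 720/12 = 60 groups, or 15 enrolled per group before 20% attrition, which is within the planned 6 to 20.

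**Formulas.**
- Design effect: DE = 1 + (m − 1) × ICC
- True one-sided error at d = 0.25 when groups are ignored: Φ(−1.645/√DE)
- Correct distance from estimate to upper bound: 1.645 × 0.0745 × √DE (the planned model always gives 0.123)
- Power of a correct analysis: Φ(0.25/(0.0745√DE) − 1.645)

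Example with m = 12 and ICC 0.05: DE = 1 + 11 × 0.05 = 1.55 and √DE = 1.245. The error is Φ(−1.645/1.245) = 9.3%, the distance is 0.153 d, and the power is 85%.

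| ICC | DE (m = 9.6 / 12) | True error | Correct distance to bound (d) | Power, correct analysis |
|---|---|---|---|---|
| 0 | 1.00 / 1.00 | 5.0% / 5.0% | 0.123 / 0.123 | 96% / 96% |
| 0.01 | 1.09 / 1.11 | 5.7% / 5.9% | 0.128 / 0.129 | 94% / 94% |
| 0.02 | 1.17 / 1.22 | 6.4% / 6.8% | 0.133 / 0.135 | 93% / 92% |
| 0.05 | 1.43 / 1.55 | 8.4% / 9.3% | 0.147 / 0.153 | 88% / 85% |
| 0.10 | 1.86 / 2.10 | 11.4% / 12.8% | 0.167 / 0.178 | 79% / 75% |

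**Sensitivity to group size.** At ICC 0.05 the error would be 7.1% if every group had 6 analysed and 11.9% if every group had 20.

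**Simulation check.** A simulation at the margin used 20,000 trials per ICC and 37 groups of 10 per arm. Ignoring groups gave errors of 4.7, 5.7, 6.4, 8.7 and 11.3% for ICC 0, 0.01, 0.02, 0.05 and 0.10. A group-level analysis stayed between 4.7 and 5.2%.

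**The case against.** The strongest reply is that the harm is conditional. A reader might infer that the bound is certainly too narrow and the 5% level certainly lost. The article does not support that: it gives no ICC, the effect is nil at zero, and it is modest at 0.01. Several features may also keep the ICC low. Make-up sessions mix membership, the booster is individual, intent-to-treat includes people who never attend, and contact amounts to four 90-minute sessions against follow-up to 12 months postpartum. This stands. It limits the size of the problem but does not show that the ICC is zero.

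A reader might also blame shared language and shared facilitators. Language is settled before individual randomisation, so on its own it does not inflate the error of the arm contrast. The same facilitators work in both arms, so their effects largely cancel unless the mix of facilitators differs by arm. What clearly matters is correlation created within a group after randomisation.

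Nor does ignoring the groups mean that the trial has only about 75 independent units. At ICC 0.05 the effective sample is 720/1.55 = 465 to 720/1.43 = 503.

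Finally, the article is a condensed text, and the wording in section 3.6.1 could be meant to describe only the repeated measures. This carries limited weight, because the levels of the primary model are stated and the groups are not among them.

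**Conclusion.** The point holds in conditional form. The stated two-level model does not match group delivery in both arms, and any positive within-group correlation in change pushes towards a false claim of non-inferiority. Over assumed ICCs of 0 to 0.10, with 720 analysed and 9.6 to 12 per group, the true one-sided error runs from 5.0% to 12.8%. It is material from about ICC 0.05 (8.4-9.3%).

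The fault lies mainly in the analysis model and not clearly in the sample size. N = 900 absorbs the correction up to an ICC of about 0.05, with 85-88% power. It would be wrong to infer that it does so throughout the range, since power falls to 75-79% at 0.10. These figures rest on 1:1 allocation, an SD of change of 1, a true difference of 0 for power and roughly equal group sizes.

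**What to change.** Account for therapy group in the primary analysis.

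- **Group definition.** Use the group first scheduled after randomisation, and keep it regardless of attendance or make-up sessions.
- **Model.** Add a random group effect on post-baseline change (a group slope or group-by-time effect), with Satterthwaite or Kenward-Roger degrees of freedom. A group random intercept alone is not enough, because it largely cancels from a contrast of change.
- **Fallback, stated in advance.** If the group variance cannot be estimated, use a cluster-robust variance by group with a small-sample correction.
- **Scope.** Apply the same approach to the completer sensitivity analysis and the EPDS analysis.

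The change needs no new participants or data collection, because first sessions are already scheduled at the baseline visit (section 3.2). It should be written down before analysis. The cost is a somewhat more complex model and a wider bound: the distance from estimate to bound grows from 0.123 d to 0.128-0.129 d at ICC 0.01, 0.147-0.153 d at 0.05 and 0.167-0.178 d at 0.10.
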